### Outcome measures

#### Primary outcomes

##### Health-related quality of life

The Short Form-36 (SF-36) is a widely used health survey questionnaire, especially for older adults to assess the health-related quality of life (HRQoL) [30]. The SF-36 consists of 36 items covering two dimensions—physical health (physical functioning, role limitations due to physical problems, role limitations due to emotional problems, and social functioning) and mental health (mental health, vitality, body pain, and general health perception). In the current study, the SF-36 (SF-36) will be used [31].

### Frailty

Physical Performance Test (PPT) is one of the tools which are used to assess the level of frailty [32]. It is usually used in several domains of physical function through the observed performance of various tasks that are important to simulate the activities of daily living of various degrees of complexity. It is a very simple test that usually requires about 10 min. It is developed in two versions including 9 and 7 item scale. In our research we will use the 9 item scale that includes 9 standardized tasks such as writing a sentence, simulated eating, turning 360 degrees, putting on and removing a jacket, lifting a book and putting it on a shelf, picking up a penny from the floor, a 50-foot walk test, and climbing stairs (scored as two items). The score range of each task is 0–4 and for 9 items it will be 36. A higher score indicates better performance [32].

### Cognitive function

The Mini-mental state examination (MMSE) is the most commonly used method to measure the level of cognitive impairment, especially in older adults. It is also regarded as an effective instrument to screen the severity of cognitive impairment at a given point in time and also to observe the cognitive changes in a person over time as well as to get information about the individual’s response to the particular treatment option [33]. It is a 10–15-minute test procedure that involves several sub-division of cognitive status, which includes memory, language, attention, orientation and also visuospatial proficiency. The score of Mini-mental state examination is calculated on a scale of 0–30 where score 24 or above is usually considered as the normal cognitive status or no cognitive impairment of the individual. The overall scorings are Severe cognitive impairment (0–17), Mild cognitive impairment (18–23) and no cognitive impairment (24–30).

### Secondary outcomes

#### *Health parameters* - *Body composition, resting heart rate & resting blood pressure*

The walking effects on participants’ health parameters, namely body composition, resting heart rate, and resting blood pressure will also be assessed. The body composition will be assessed by Tanita MC780U (Tanita Corporation, 2020), by which the percent body fat and lean body mass of participants will be recorded. The body mass index (BMI) using participants’ heights and weights (measured by the RA) will also be recorded. The wrist-worn Fitbit Charge 3 will be used to record the resting heart rate of participants (also the heart rates during walking in reflecting the exercise intensity of the participants as well as the accumulated footsteps and the duration of the completed footsteps during each session of the intervention for performance analyses). The resting blood pressure of the participants will be recorded by Lenus Automatic Blood Pressure Monitor DP65. All the assessments will be conducted in the pre-test, post-test and follow-up test for comparisons.

### Physical activity enjoyment

The 8-item Physical Activity Enjoyment Scale (PACES)[34] will be applied to measure the participants’ level of enjoyment after engaging in walking intervention programs. The 8-item Physical Activity Enjoyment Scale is rated by a 7 bipolar rating, with items such as " I enjoy it.“ (One extreme) to " I dislike it.“(the other extreme). In the scale, the negative items (i.e., 1, 4, 5, and 7) requires reverse coding, and the Higher PACES score the greater levels of physical activity enjoyment demonstrated. The 8-item PACES showed excellent internal consistency and reliability among the older adult population. Furthermore, the scale showed adequate validity and show no measurement invariance between genders.

#### Walking performance

The time for completing the targeted steps in targeted heart rate zones of each participant in each training session will be recorded for analysis of performance and improvement on walking. All the data will be recorded by the wrist-worn Fitbit Charge 3 and retrieve from the computer after each training session. .

### Intervention experience evaluation

To further investigate and compare the perception of the participants after the intervention, a few open-ended questions regarding their feelings and attitude towards the intervention, as well as their physical activity behavior after the intervention will be asked in the follow-up test. (Please refer to Appendix for the examples of the questionnaire items)

### Statistical analysis

Descriptive statistics will be used to describe baseline characteristics such as gender, age, living status (alone or with family), body height, body weight, resting heart rate, and blood pressure of the participants in the study. The primary outcomes will be analyzed using an intention-to-treat (ITT) approach, and a sensitivity test will subsequently be conducted using the available data. Missing data will be replaced using the last observation carried forward method. For the secondary outcomes, a per-protocol analysis will be conducted using the available data. The statistical significance level was set at *p* < .05. All data will be analyzed using SPSS Version 26.0 (IBM, Chicago, IL). For the within-group test, a one-way repeated measure analysis of variance (ANOVA) will be applied to each group to determine the changes of each outcome parameter among the three-time points (i.e., pretest, posttest, and follow-up test). When the sphericity assumption was violated, the Greenhouse– Geisser correction will be used when epsilon < 0.75, or the Huynh–Feldt correction will be used when epsilon > 0.75. Post hoc analysis with Bonferroni correction will be conducted to explore the differences between the pretest and posttest, as well as posttest and follow-up test. The mean differences with 95% confidence intervals (CIs) will be reported. For the inter-group test, a one-way analysis of covariance (ANCOVA) with the baseline value as a covariate will be conducted at the posttest, and follow-up test to determine the group effect on each outcome parameter. Subsequently, the differences between the intervention groups and the control group will be analyzed through planned contrasts.

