## Methods

### Study design

This study will apply a three-group (2 intervention groups and 1 control group), double-blinded (outcome assessors and data analysts), randomized controlled trial (RCT) to compare the effects of supervised group-based walking and non-supervised individual-based walking interventions on frailty, cognitive function and quality of life among older adults in the Kingdom of Saudi Arabia, immediately after a 16-week intervention, and 12-week residual effects after completion of the intervention. The double blinding adopted in this study is to reduce the bias and to ensure that those who are collecting the outcome measures (such as research assistants collecting data via questionnaires), and those who are inputting and analyzing the data, have no knowledge regarding group allocation status of the study participants. In assigning the groups, the CONSORT procedure will be followed [26]. The intervention groups will participate in a group-based walking intervention with professional trainer’s supervision and an individual-based walking intervention without professional trainer's supervision whereas the control group will not receive training but will be provided opportunity to receive the same training after the final assessment (12-week after completion of the intervention). This offer will be an incentive to the participants staying in the control group until the completion of the project. The study will be conducted following the international Good Clinical Practice Guidelines, by which the approval from the Research Ethics Committee of the Hong Kong Baptist University will be received prior to the commencement of the study.

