### Sample size estimation

G*Power was used to determine the sample size. Based on the previous intervention studies, the most frequently reported effect size was ranged from moderate (0.25) to high (0.70) [28, 29], a moderate effect size of 0.25 will be adopted for the current study. To ensure a power of 80% probability for detecting a treatment difference at a two-sided 5% level of significance, a sample size of 35 participants per group (total 105 for 3 groups) is expected to recruit. Yet, considering a 20% of potential dropout rate, a sample size of 42 participants per group (total 126 for 3 groups) will be required in the current study for the two-way repeated measures in three-time points. It is decided a total of 126 participants will be recruited. In order to satisfy the culture of KSA that males and females should undergo walking intervention separately in the group, an equal number of males and females (63 M and 63 F) will be recruited and randomly and equally assigned to the two intervention groups and control group. Moreover, in order to have an approximate mean age in each intervention group, the participants will be divided into 2 groups (60–64 and 65 to 70) for the randomization.

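### Carrying the last observation forward in the primary analysis biases the posttest and 12-week estimates by an amount that depends on when, and from which arm, participants leave

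*Protocol article*

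**What the plan says.** All of the analysis text is in the protocol article, Statistical analysis.

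- Analysis set: "The primary outcomes will be analyzed using an intention-to-treat (ITT) approach, and a sensitivity test will subsequently be conducted using the available data".
- Missing values: "Missing data will be replaced using the last observation carried forward method". No assumption about why data are missing, and no justification, is given.
- Between-group test: "a one-way analysis of covariance (ANCOVA) with the baseline value as a covariate will be conducted at the posttest, and follow-up test".
- Intervals: "The mean differences with 95% confidence intervals (CIs) will be reported".

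Study design sets the aim as effects "immediately after a 16-week intervention, and 12-week residual effects after completion of the intervention". The assessments are therefore pretest, posttest at week 16 and one follow-up 12 weeks later. Sample size estimation plans 42 per group, "considering a 20% of potential dropout rate". It gives no timing for the dropout and no split by arm.

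**The concern.** This is a stated choice for the three primary outcomes, not a detail left to a later document. With three visits the rule can do only two things. A participant who leaves during training has the pretest value entered at posttest and again at follow-up, so the change is zero. A participant who leaves after posttest has the posttest value entered at follow-up, so whatever was gained is taken as fully kept.

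The second case matters most here, because whether the gain is kept is what the follow-up visit is meant to find out. The same values enter the within-group comparison of posttest with follow-up. There each late dropout contributes a zero difference, so with 20% late dropout a true decline d is estimated as about 0.8d.

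The expected exposure is not small: 20% of 126 is about 25 participants. Unequal dropout is also plausible, since the walking arms attend three sessions a week for 16 weeks while controls keep logs. Zero change is then imputed more often in one arm than in another.

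**Working it through.** **Inputs from the document.** 42 per group; 20% dropout; ANCOVA on baseline at each later visit; 95% intervals.

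**Assumed, because the document gives no value.** SD 1; correlation 0.6 between any two visits; true posttest effect 0.5 SD; follow-up effect 0 or 0.25 SD; dropout unrelated to outcome; timing varied. The plan says "a moderate effect size of 0.25 will be adopted for the current study". Read as Cohen's f, that equals 2 × 0.25 = 0.5 SD between two equal groups, which is why 0.5 was used.

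**The plan's own figure.** For the between-groups test in repeated measures, λ = f²·N·m/[1 + (m − 1)ρ]. With m = 3 and an assumed ρ = 0.5, N = 105 gives λ = 0.0625 × 105 × 3/2 = 9.84 and power 79.7%. The formula asks for 108, so 105 is reproduced within 3%. The planned 126 is 105 × 1.2.

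**Expected estimates.** Let *e* be the share lost before posttest, *l* the share lost between posttest and follow-up, and δ₁ and δ₂ the true effects at posttest and follow-up. With equal dropout across arms:

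- posttest estimate = (1 − e)·δ₁
- follow-up estimate = (1 − e − l)·δ₂ + l·δ₁

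All early (e = 0.2): posttest 0.8 × 0.5 = 0.40. Split (e = l = 0.1): posttest 0.9 × 0.5 = 0.45.

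Follow-up with the effect fully lost: all late gives 0.2 × 0.5 = 0.10; split gives 0.1 × 0.5 = 0.05.

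Follow-up with a true effect of 0.25, split: 0.8 × 0.25 + 0.1 × 0.5 = 0.25, so the two biases cancel.

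**Unequal dropout, no true effect.** If both arms gain 0.4 SD on retest and lose 10% and 30% early, the estimate is 0.9 × 0.4 − 0.7 × 0.4 = 0.08 SD. With a gain of 0.3 SD it is 0.06 SD.

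**Standard error at posttest, all dropout early.** The slope on baseline becomes 0.8 × 0.6 + 0.2 = 0.68. The residual variance is 1 − 0.68² = 0.5376 in the arm without effect. In the arm with effect it is 0.5376 + 0.2 × 0.8 × 0.5² = 0.5776. SE = √[(0.5376 + 0.5776)/42] = 0.163. Available-case ANCOVA gives √[2 × (1 − 0.6²)/33.6] = 0.195.

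**Coverage.** Bias/SE = 0.10/0.163 = 0.61, so coverage of the true effect is Φ(1.96 − 0.61) − Φ(−1.96 − 0.61) ≈ 0.91. The shift in the estimate accounts for the whole shortfall.

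**Simulation** (6,000 two-arm trials per scenario; LOCF = last observation carried forward):

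| Dropout | Visit, true effect | LOCF estimate | LOCF mean SE (actual spread) | LOCF coverage | Available-case estimate, SE |
|---|---|---|---|---|---|
| 20% early | posttest, 0.50 | 0.40 | 0.163 (0.164) | 90–91% | 0.50, 0.196 |
| 10% early, 10% late | posttest, 0.50 | 0.45 | 0.170 (0.171) | 93.6% | 0.50, 0.185 |
| 20% early | follow-up, 0.25 | 0.20 | 0.161 (0.162) | 93.6% | 0.25, 0.196 |
| 10% early, 10% late | follow-up, 0.25 | 0.245 | 0.169 (0.170) | 94.9% | 0.245, 0.197 |
| 10% early, 10% late | follow-up, 0 | 0.05 | 0.170 (0.170) | 94.0% | not tabulated |
| 20% late | follow-up, 0 | 0.10 | 0.178 (0.179) | 91% | 0.00, 0.196 |

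False positives at follow-up when the effect is fully lost are 8.4–8.6% with all dropout late (available cases 4.4–5.3%) and 6.0% with split dropout. For 10% v 30% dropout and no effect they are 6.8% at a common gain of 0.3 SD and 8.2% at 0.4 SD. With equal random dropout and no effect, LOCF rejects at 5.1%, as it should.

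**The case against.** **A safeguard is already planned.** The sentence just before the LOCF rule provides an available-data analysis of the primary outcomes. With the effect lost and all dropout late, it would show about 0.00 beside LOCF's 0.10, so a careful reader would see the distortion. This stands, and it would be wrong to say that nothing is planned. But that test is the sensitivity analysis, the headline estimate stays with LOCF, and no rule says which prevails if they differ.

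**The direction at follow-up is not fixed.** A reader might infer that LOCF always favours a maintained effect. It does so only for late dropout; early dropout carries the baseline forward and pulls the effect down. The document does not say when dropout is expected, so only a range can be given, and that range includes full cancellation.

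**Intervals too narrow.** A reader might infer from the smaller standard error that LOCF understates its own uncertainty. It does not in these scenarios: the mean SE matches the actual spread of the LOCF estimate (0.163 against 0.164). The intervals miss the true effect because they are centred in the wrong place.

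**Unequal dropout is hypothetical.** The plan assumes one rate, offers controls later training as an incentive to stay, and gives a voucher for completion. The 10% v 30% case is an illustration, not a forecast.

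**Who would be imputed is unclear.** The section on the walking prescription limits the analyses to participants with at least 70% attendance. If that rule governed, many early leavers in the walking arms would be excluded rather than imputed. That conflict with intention to treat is a separate matter, but it limits how firmly the early-dropout figures apply.

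**Conclusion.** The point holds as a matter of bias. The primary rule sets early leavers to no change and late leavers to full persistence, and the second builds in an answer to the residual-effect question.

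Under the stated assumptions, a 0.5 SD posttest effect is reported as 0.40 to 0.45, with coverage of about 90–91% to 94%. A vanished effect is reported at follow-up as 0.05 to 0.10 SD, with false positives of about 6% to 8.6%. Unequal dropout with a common retest gain creates a spurious difference of about 0.06 to 0.08 SD.

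The SD, correlation, effect and dropout timing are not in the document, so these sizes are illustrative; 0.40 and 0.10 come from the extremes of timing. Since timing and arm of dropout cannot be known in advance, LOCF cannot be defended as conservative. The material does not support saying that the bias always favours persistence, or that the LOCF standard error is itself in error.

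**What to change.** Make the primary analysis a likelihood-based linear mixed model for repeated measures:

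- all randomised participants, with posttest and follow-up values as outcomes;
- fixed effects for arm, time, arm-by-time, baseline value and baseline-by-time;
- unstructured covariance and no single imputation;
- arm contrasts at posttest and at follow-up read from this one model.

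State that the model assumes data missing at random given what was observed. Drop LOCF, or keep it only as a sensitivity analysis. Multiple imputation would also serve.

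The cost is analysis wording only: the MIXED procedure in the SPSS package already named fits this model, and no further participants, visits or data are needed. The downside is a somewhat larger standard error: at posttest about 0.185–0.196 against 0.163–0.170 under LOCF, taking available-case ANCOVA as a guide.

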To compare the difference of effects between supervised group-based walking and non-supervised individual-based walking on the primary outcomes, including frailty, cognitive functions, and health-related quality of life among inactive older adults in Saudi Arabia.To compare the difference of effects between supervised group-based walking and non-supervised individual-based walking on the secondary outcomes, including physical activity enjoyment, health parameters consisting of resting heart rate, resting blood pressure, and body composition, as well as walking performance among inactive older adults in Saudi Arabia.To formulate guidelines for achieving an effective walking intervention for inactive older adults in Saudi Arabia.To recommend the government of Saudi Arabia on guidelines and policies for promoting walking and active ageing among older adults in the country.

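### Three primary outcomes are each tested between groups at two visits at p<.05, with no deciding outcome or visit and no adjustment of these tests, so 5% does not bound the chance of a false primary claim

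*Protocol article*

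**What the plan says.** The first objective, printed at the end of the section on benefits of group-based physical activity, sets out "the primary outcomes, including frailty, cognitive functions, and health-related quality of life" together, with no ranking. The outcome sections assign the SF-36, the 9-item PPT and the MMSE to them. On the SF-36 the article says "The SF-36 consists of 36 items covering two dimensions", physical and mental health, and does not say which score decides.

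The Statistical analysis section gives one level for everything: "The statistical significance level was set at" p < .05. For the comparison between groups it plans a one-way ANCOVA adjusted for baseline, run at the posttest and "follow-up test to determine the group effect on each outcome parameter". Planned contrasts of the intervention groups with control come next. Bonferroni appears once in that section, for the post hoc pretest–posttest and posttest–follow-up differences within a group.

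The Sample size estimation section works "at a two-sided 5% level of significance", so the whole 5% is used and no share is set aside for several primary tests.

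**The concern.** In a randomised trial the between-group tests carry the evidence on treatment. Here the correction protects the within-group changes and leaves the between-group primary tests uncorrected. With three outcomes, two visits and nothing marked as deciding, there are at least six chances to obtain p < .05 on a primary outcome.

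The objectives include guidelines for walking interventions and recommendations to government, and the Discussion expects the results to justify policy and resources. A reader who sees one significant primary result would take its error rate to be 5%. Unless it is settled beforehand which result decides, that is not so.

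**Working it through.** **Inputs from the article.** Three primary outcomes; two post-baseline visits with a separate ANCOVA at each; α = 0.05 per test; 35 per group (105 in total) before dropout; effect size 0.25; 80% power; three groups and three time points.

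**Assumed inputs.** The article gives no correlations between outcomes or between visits, so a range is used.

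**1. The plan's own sample size.** Read 0.25 as Cohen's f and take the between-groups test of a repeated-measures ANOVA, with k = 3 groups, m = 3 times and an assumed correlation between times of ρ = 0.5:

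λ = f²·N·m / (1 + (m − 1)ρ) = 0.0625 × 105 × 3 / 2 = 9.84, with 2 and 102 degrees of freedom.

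Power at α = 0.05 is 79.7%, and the smallest N (in multiples of 3) for 80% is 108. The stated 105 is therefore reproduced closely, at the full 5%.

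**2. Error rate if the tests are independent,** 1 − 0.95^k:

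| Family of overall between-group tests | k | Chance of at least one false positive |
|---|---|---|
| One outcome, both visits | 2 | 9.75% |
| Three outcomes, posttest only | 3 | 14.3% |
| Three outcomes, both visits | 6 | 26.5% |
| SF-36 as two dimensions, both visits | 8 | 33.7% |

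**3. Error rate if the tests are correlated.** Three-group F tests were simulated with no true effect and 35 per group:

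| Assumed correlation, outcomes / visits | 6 tests | 8 tests |
|---|---|---|
| 0.3 / 0.6 | 23.4% | 29.7% |
| 0.5 / 0.7 | 20.7% | 25.4% |
| 0.6 / 0.8 | 18.2% | 22.3% |

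With posttest only and 0.3 between outcomes, three tests give 13.8%.

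**4. Price of control.** With λ = 9.84 as in step 1, power at N = 105 is 65.0% at α = 0.05/3 = 0.0167, against 79.7% at 0.05. Regaining 80% at 0.0167 needs N = 141 before dropout. Holm tests only the smallest p-value at 0.0167. After a rejection the next is tested at 0.025 and the last at 0.05, so 65% applies to the first step.

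**The case against.** - **An unseen analysis plan may settle it.** A testing order, the lead SF-36 score and the handling of contrasts are often left to such a plan, so the article does not show that the trial has no hierarchy. That stands. But the article does fix the level, the tests, the visits and where correction applies, and it sizes the trial at the full 5%. A later split of α would depart from that basis.
- **No rule says that any one result is enough.** True, and frailty, cognition and quality of life can be argued to be separate claims at 5% each. A reader might infer an explicit any-one-wins rule, but the article states none, so the figures are conditional on that use. Even as separate claims, each outcome has two undesignated visits (9.75% if independent).
- **The visits have a natural order.** The design speaks of effects immediately after the intervention and then of residual effects, which suggests posttest first. If that were made explicit, the figure would be about 14%: about half, and still well above 5%.
- **Eight tests is only one reading.** Agreed. The article describes two SF-36 dimensions and does not say that both are tested as primary. Six is the minimum.
- **The versus-control contrasts could be added to the count.** Read at .05 regardless of the ANCOVA, they would give about 34–54%. The article has them follow the ANCOVA, which can be read as testing them only after a significant overall result. At correlations 0.3 and 0.6 the chance of any false contrast is then about 20% for three outcomes, below the overall-test figure. The higher range is not relied on.

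**Conclusion.** The point holds for the between-group tests of the primary outcomes. It would be wrong to say that the plan has no multiplicity correction at all, because the within-group comparisons over time have one.

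If any one primary result can carry the claim, the chance of at least one false positive among the six overall tests is 26.5% under independence and about 18–23% under assumed moderate to high correlation. No single value can be drawn from the article, because it gives no correlations. Under every reading examined, including posttest alone, the figure is well above 5%, so the conclusion does not depend on the assumed values.

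**What to change.** Before unblinding:

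1. Designate posttest as the primary time point and name one SF-36 score as primary.
2. Either apply Holm at an overall 0.05 across the three primary between-group tests (PPT, MMSE and that SF-36 score), or name one primary outcome and make the other two secondary.
3. Label follow-up, the other SF-36 scores and the remaining contrasts as secondary, with unadjusted 95% confidence intervals.
4. As a separate correction, add the contrast between supervised group walking and non-supervised individual walking and use it as the primary between-group test. It is the stated objective, but the Statistical analysis section lists only contrasts with control.

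**Cost.** No new data are needed, but the loss of power should be stated. At Holm's first step, power on the protocol's own design (f = 0.25, N = 105, ρ = 0.5 assumed) falls from about 80% to about 65% per outcome. Naming a single primary outcome at posttest avoids that loss.

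These figures are for the three-group test behind the sample size and do not carry over to the contrast in item 4, whose power should be worked out separately. As an illustration, assume a standardised difference of 0.5, 35 per arm and no baseline adjustment. The noncentrality is then 0.5 × √(35/2) = 2.09 on 68 degrees of freedom, and power is about 54% at 0.05 and about 36% at 0.0167. Adjustment for baseline would raise both by an amount that the article gives no basis to estimate.

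### The available-data analyses leave observed visits unused: the repeated-measures ANOVA drops anyone missing a visit, and the follow-up ANCOVA ignores posttest values

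*Protocol article*

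**What the plan says.** Everything on this point is in the Statistical analysis section of the protocol article.

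- **Primary outcomes:** intention-to-treat. "Missing data will be replaced using the last observation carried forward method", and "a sensitivity test will subsequently be conducted using the available data".
- **Secondary outcomes:** per-protocol, also on available data, with no imputation.
- **Within-arm model:** "a one-way repeated measure analysis of variance (ANOVA) will be applied to each group to determine the changes of each outcome parameter", over pretest, posttest and follow-up. Bonferroni comparisons of pretest with posttest and of posttest with follow-up come after it. Mean differences with 95% confidence intervals are to be reported.
- **Between-arm model:** ANCOVA with the baseline value as covariate, run once at posttest and once at follow-up, then planned contrasts of the intervention arms with control.
- **Software:** SPSS 26.

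No other model is named for the sensitivity test or the secondary outcomes. Sample size estimation plans for loss: "considering a 20% of potential dropout rate", it arrives at 42 per group, 126 in total.

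**The concern.** The data set and the methods do not fit each other. Classical repeated-measures ANOVA needs a complete row for each participant. Someone assessed at pretest and posttest who misses follow-up therefore leaves the pretest-posttest comparison too, although both values were observed. The follow-up ANCOVA conditions on baseline only, so it cannot use what the posttest says about those who did not return. The within-arm pretest-posttest change and the posttest ANCOVA also end up describing different sets of people.

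This affects two things. For the primary outcomes, the available-data run is the only check on LOCF. For the secondary outcomes, it is the only analysis. If people leave according to how they were doing at posttest, both can mislead, although the data needed to reduce the problem will have been collected.

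**Working it through.** **1. The plan's own figure.** Inputs from Sample size estimation: effect size 0.25 (read as Cohen's f), two-sided 5%, 80% power, three groups, three time points. Assumption: between-visit correlation 0.5, since the protocol gives none. For the between-groups test of a repeated-measures ANOVA, λ = f²·N·m / (1 + (m−1)ρ).
- At N = 105: λ = 0.0625 × 105 × 3 / 2 = 9.84 on 2 and 102 degrees of freedom; power 0.797.
- The smallest balanced N reaching 80% is 108, within 3% of the stated 105.
- The stated 42 per group is 35 × 1.2.

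The planning figure is thus reproduced closely enough. What matters below is the 20% loss.

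**2. Observed visits left unused.** 20% of 126 = 25.2, about 25 people.

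| Timing of loss | Observed visits dropped by ANOVA | Lost to posttest ANCOVA | Lost to follow-up ANCOVA | Observed posttests unused at follow-up |
|---|---|---|---|---|
| All before posttest | about 25 (pretests) | 25 | 25 | 0 |
| Half and half | about 38 | 13 | 25 | 13 |
| All after posttest | about 50 (pretests and posttests) | 0 | 25 | 25 |

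**3. Cost if loss is random.** No bias arises. The pretest-posttest change is estimated from 80% of participants although more have both values.
- Half of the loss after posttest: √(0.9/0.8) = 1.06, a standard error 6% larger.
- All of the loss after posttest: √(1/0.8) = 1.12, 12% larger.

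**4. Bias if loss is selective.** Large-sample simulation, 400,000 per arm. Assumptions, none of them from the protocol: correlation 0.5 or 0.7; true walking effect 0.50 SD at posttest and 0.30 SD at follow-up; 10% or 20% lost after posttest; in walkers, log-odds of loss 0.5 or 1.0 higher per SD of poorer change; in controls, loss at random.

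| Quantity | Truth | Planned method | Method using the posttest |
|---|---|---|---|
| Walkers' pretest-posttest change (ANOVA completers) | 0.50 | 0.53-0.68 | – |
| Follow-up contrast with control (ANCOVA) | 0.30 | 0.31-0.35 | 0.30 |

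The lower end of the first row is 0.53/0.50 = 1.06; the upper end is about 1.35. The second row is a bias of about 0.01-0.05 SD. With 42 × 0.8 ≈ 34 per arm, the standard error of that contrast is √(2(1−r²)/34), which is 0.21 at r = 0.5 and 0.17 at r = 0.7. The bias is therefore at most about a quarter of a standard error.

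**5. Where the follow-up ANCOVA is and is not biased.** A second simulation assumed a true effect of 0.50 SD at both visits, correlation 0.5, 20% missing at follow-up only and a steeper dependence (logistic slope 1.5).

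| Loss depends on | Available-case ANCOVA | LOCF | Likelihood-based |
|---|---|---|---|
| Nothing | 0.50 | 0.50 | 0.50 |
| Baseline | 0.50 | 0.50 | 0.50 |
| Posttest, same in both arms | 0.50 | 0.50 | 0.50 |
| Posttest, treated arm only | 0.56 | 0.41 | 0.50 |
| Unobserved follow-up, treated arm only | 0.67 | 0.59 | 0.66 |

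The posttest ANCOVA gave 0.50 throughout. The within-arm change among ANOVA completers (truth 0.50) was 0.39 under baseline-dependent loss and 0.61 under posttest-dependent loss, so its error can go either way.

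**6. What the check can show.** Under the step 4 assumptions at correlation 0.5 and 20% loss, with log-odds 1.0, LOCF gave 0.27 and the available-case ANCOVA 0.35 (truth 0.30). With log-odds 0.5, LOCF gave 0.30 and the available-case ANCOVA 0.32. In the first case both are off, on opposite sides; in the second only the check is off. The gap alone does not distinguish these cases.

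**The case against.** A reader might infer several stronger things that the document does not support.

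- **That both methods discard all visits of anyone who misses one.** This is true of the ANOVA only. The posttest ANCOVA keeps everyone with baseline and posttest, and the follow-up ANCOVA keeps those who missed only the posttest.
- **That the check is biased as such.** The between-arm estimate is biased only if loss depends on posttest differently by arm, or on unobserved values. The protocol does not predict such loss. Retention incentives do differ: controls are offered later training as a reason to stay, and the voucher carries an attendance condition for walkers. That makes arm-dependent loss credible, not established.
- **That the treatment effect is overstated by up to a third.** That range is a within-arm change. The between-arm bias is 0.01-0.05 SD, and it would be smaller between the two walking arms, the protocol's stated comparison, unless their dropout patterns differ.
- **That the sensitivity test can show nothing.** It can diverge from LOCF and so signal that missing data matter. It cannot say which estimate to believe.
- **That the main primary analysis suffers.** After LOCF there are no empty cells, so no one is dropped there for a missed visit.

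All five corrections stand. Two further objections weigh less. A fuller plan might name another model for the sensitivity test, but the article applies the ANOVA and ANCOVA to each outcome parameter and names nothing else. A mixed model also gains little under loss that depends on unobserved values (0.66 against 0.67), but it did no worse under any pattern examined.

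**Conclusion.** The concern holds in limited form. The methods named for the available-data analyses cannot use all the available data: about 25 to 50 observed visits drop out of the ANOVA at the planned 20% loss, and up to 25 observed posttests go unused at follow-up.

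- **Random loss:** no bias; a within-arm pretest-posttest standard error 6-12% larger.
- **Walkers with poor change leaving more often:** within-arm change about 6-35% too large, follow-up contrast with control about 0.01-0.05 SD too large. The upper ends assume that all 20% are lost after posttest and that the dependence is strong; the protocol gives neither timing nor reasons for dropout.

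The between-arm distortion is small beside its sampling error. The change is still worth making, because this is the only check on LOCF for the primary outcomes and the only analysis of the secondary ones, and a better method is available in the named software.

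**What to change.** For the available-data sensitivity analysis, and for secondary outcomes measured at all three visits in the arms compared, replace the separate ANOVAs and single-visit ANCOVAs with one likelihood-based linear mixed model per outcome (SPSS MIXED):

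- Pretest, posttest and follow-up all enter as responses, with every observed visit used.
- Terms are arm, visit and arm-by-visit, with baseline means constrained equal across arms. This constraint takes the place of a baseline covariate, since pretest cannot be both response and covariate in one model.
- The covariance matrix is unstructured, so the sphericity step is no longer needed.
- The within-arm contrasts (pretest to posttest, posttest to follow-up) and the between-arm contrasts at each later visit, including supervised group against non-supervised individual walking, all come from this model.

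Leave walking performance, which is recorded per training session and not in controls, to its own analysis. Apply the model to the enjoyment scale only if it is measured at all three visits in the arms compared.

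**Cost:** revised wording and a few lines of syntax; no new data; slightly more modelling work. The model does not correct loss that depends on unobserved values, nor the selection that comes from the per-protocol restriction.
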